The purpose of this prospective, randomized controlled study is to compare the incidences of acute urinary retention and UTI in patients having catheter removal at 2 days and 7 days after laparoscopic anterior resection and thus establish the optimal time for catheter removal. The primary outcome measure is the incidence of urinary retention. The secondary outcome measures are the incidence of UTI, time of off-bed activity, and subjective discomfort. The study protocol has been written in accordance with the Standard Protocol Items: Recommendations for Interventional Trials (SPIRIT) checklist (Additional file 1).

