### Outcome measures

#### Primary outcome measures

Postoperative urinary retention requiring recatheterization following urethral catheter removal.

Acute postoperative urinary retention is defined as > 100 ml postvoid residual urine demonstrated on bladder ultrasound, with need for recatheterization within 1 day of removal of the urethral catheter [2].

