### Randomization and blinding

Patients will be randomized to the study group and the control group with an allocation ratio of 1:1. Randomization will be done using random numbers generated with Statistical Analysis System (SAS) software. A central randomization system will be employed. All of the researchers will register on the website of the research system. When a researcher has chosen a certain patient, he/she will log in to the webpage and upload the basic information on the patient. The group allotment will then be revealed.

All patients will be undergoing the same (similar) surgery. The only difference will be the catheter removal time. Obviously, it is impossible to blind the surgeons who will perform the operations. However, all surgeon researchers will be required to limit potential cointerventions as much as possible. Result assessment will be made by independent researchers blinded to the surgical procedures.

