### Grouping

All participants will undergo urethral catheter insertion after placement of the epidural catheter for analgesia. After urethral catheter placement the participants will be randomly assigned to either the experimental arm or the control arm.

Participants assigned to the experimental arm will have their urethral catheters removed on postoperative day 2, and participants assigned to the control group will have their urethral catheters removed on postoperative day 7. In both groups, catheter removal will be done when the bladder is distended; this is standard practice in our institution. Control group patients will practice intermittent catheter clamping from postoperative day 4 onward.

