### Detailed description of procedure

Catheterization will be performed using all aseptic precautions. The investigator will ensure that the drainage bag is positioned intraoperatively and postoperatively. The drainage tube ends and drainage bags will not be higher than the pubic symphysis, and will be kept unobstructed. The urethra, urethral orifice, and perineum will be kept clean when removing the catheter so that a clean midstream urine sample can be collected for urine routine examination and culture. The catheter retention duration will be recorded, and also the first self-urination time, residual urine, pain score, and recatheterization (if any).

For all patients the catheter will be clamped for some time so that the bladder is full when the catheter is removed. The catheter will be pulled out when the desire for urination is at a peak and bladder pressure is increasing. These measures are conducive to the recovery of bladder function and establishment of an effective micturition reflex, which can effectively shorten the time to first micturition after catheter removal.

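### Only the control arm has multi-day catheter clamping, although removal time is called the only difference between arms, so a difference in retention cannot be attributed to removal time alone

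*Protocol article*

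**What the plan says.** All places are in the protocol article.

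- **Aim (Background).** The trial compares retention and urinary tract infection after removal at 2 and 7 days, to "thus establish the optimal time for catheter removal". The abstract describes the arms by removal day only.
- **Difference between arms (Randomization and blinding).** "The only difference will be the catheter removal time". The same paragraph adds that "all surgeon researchers will be required to limit potential cointerventions as much as possible".
- **Arms (Grouping).** "Participants assigned to the experimental arm will have their urethral catheters removed on postoperative day 2"; the control arm's come out on day 7. Then: "Control group patients will practice intermittent catheter clamping from postoperative day 4 onward".
- **Clamping in both arms (Detailed description of procedure).** "For all patients the catheter will be clamped for some time so that the bladder is full when the catheter is removed". Of this clamping, and of withdrawing the catheter when the urge to void is strongest, the section says: "These measures are conducive to the recovery of bladder function and establishment of an effective micturition reflex".
- **Primary outcome (Primary outcome measures).** "Postoperative urinary retention requiring recatheterization following urethral catheter removal", with the need for a new catheter arising within 1 day of removal.

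**The concern.** The statement in Randomization and blinding and the one in Grouping cannot both be true. One says the arms differ in one respect; the other introduces a second difference, in how the bladder is managed during the days before control patients reach the primary outcome.

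The trial's stated product is a conclusion about timing. If the arms also differ in clamping, the trial compares two packages: day-2 removal, and day-7 removal preceded by intermittent clamping from day 4. A reader told that timing was the only difference would apply the result to units that remove catheters on day 7 without such clamping, and the trial holds no data on that practice.

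**Working it through.** **1. The plan's own figure, for context.** Inputs from Study design: 25% retention with early removal, 10% with late removal, α = 0.05, β = 0.2; two-sided testing from Statistical analysis. With the pooled-variance formula and mean rate (0.25 + 0.10)/2 = 0.175:

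n = [1.960·√(2·0.175·0.825) + 0.842·√(0.25·0.75 + 0.10·0.90)]² / 0.15²
= [1.960·0.537 + 0.842·0.527]² / 0.0225
≈ 2.24 / 0.0225 ≈ 99.5, rounded up to **100 per group**.

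This matches the article (power at 100 per group is 80.2%). The point below does not change it.

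**2. What each arm receives.**

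| | Day-2 arm | Day-7 arm |
|---|---|---|
| Clamp before removal, bladder full | yes | yes |
| Intermittent clamping from day 4 | none stated; catheter already out | yes, about 7 − 4 = 3 days |
| Catheter removed | day 2 | day 7 |

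Two rows differ, not one. The second row coincides with allocation for every patient treated as planned.

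**3. What the trial can estimate.** Let E be the retention rate with day-2 removal, L the rate with day-7 removal plus clamping, and U the rate with day-7 removal without the multi-day clamping. Then

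E − L = (E − U) + (U − L),

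where E − U is the effect of timing alone and U − L is the effect of clamping. The trial observes E and L. No arm observes U, so any value of U fits the same data, and no adjustment of the analysis can recover the split.

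**4. Direction.** The article gives no clamping effect, so its sign is an assumption.

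- If clamping lowers retention, U − L > 0 and the observed E − L is larger than the timing effect E − U. The bias runs against early removal.
- If the trial then shows less retention with early removal (E − L < 0), the timing effect E − U is more negative still, so that conclusion is conservative.
- If the trial shows more retention with early removal (E − L > 0), the timing effect could be smaller, zero or reversed. This is the result open to the clamping explanation. It is also the direction of the planning rates (25% early, 10% late).
- If clamping raises retention, these statements reverse.

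**5. Does the article say that clamping affects retention?** Not for repeated clamping. The benefit claimed in Detailed description of procedure belongs to the clamp before removal and full-bladder withdrawal, which both arms receive, and the concrete gain it names is a shorter time to first voiding. The Discussion's argument about bladder pressure also concerns removal with a distended bladder. Extending either to several days of clamping is reasonable, but it is an inference.

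**The case against.** The strongest reply is that this is an ordinary randomized comparison of two strategies. Clamping from day 4 needs a catheter in place on day 4, so that schedule can exist only in the late arm, and a pragmatic trial may compare late removal as a package. This stands: the randomized contrast is valid for the packages. It does not rescue the text, because the article describes a comparison of times, and clamping is not inherent in later removal. Nor does the article call the day-4 clamping standard practice; that remark in Grouping covers removal with a distended bladder.

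Three stronger readings are tempting, and the article does not support them.

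- *That a retention difference says nothing about removal time.* Timing is part of the contrast. What is lost is attribution to timing alone.
- *That by the plan's own reasoning clamping acts on the primary outcome in one arm only.* The measures it credits are given to both arms. Nor does it say that day-2 patients are clamped only once; it gives neither number nor duration for the clamp before removal.
- *That a known share of the planned 15 points (25% − 10%) is due to clamping.* This would need an invented clamping effect, and would treat the 10% planning rate as coming from clamped patients. The article does not say that they were.

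**Conclusion.** The contradiction is real, and nothing else in the article resolves it. The statement that removal time is the only difference is wrong as written. The trial can support a conclusion about the two strategies, but not about removal time in isolation.

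The size of the clamping contribution is not identifiable, so no figure is given. The contradiction and the non-identifiability rest on the text alone. The view that the bias matters rests on the assumption that repeated clamping affects retention, and the view that it runs against early removal rests on the further assumption that it lowers it. Under both assumptions, mainly a result favouring late removal would be in doubt, while one favouring early removal would be conservative.

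**What to change.** Reconcile Randomization and blinding with Grouping. If practice stays as written:

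- correct the sentence on the only difference so that it names the control arm's intermittent clamping;
- state the objective, in the Abstract and Background, and the eventual conclusion as a comparison of two catheter-management strategies: day-2 removal versus day-7 removal with intermittent clamping from day 4;
- make no claim about removal time alone.

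Whether to change the clamping practice is for the clinical team, and no view is taken here. A per-patient record of clamping would help to describe the strategies as delivered, but the full protocol or case report form may already provide it, so its absence from the article is not counted as a defect.

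The cost is a small wording amendment, in a trial that is already registered, ethically approved and recruiting, and a narrower claim. Sample size, randomization and the primary analysis do not change.

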### Detailed description of procedure

Catheterization will be performed using all aseptic precautions. The investigator will ensure that the drainage bag is positioned intraoperatively and postoperatively. The drainage tube ends and drainage bags will not be higher than the pubic symphysis, and will be kept unobstructed. The urethra, urethral orifice, and perineum will be kept clean when removing the catheter so that a clean midstream urine sample can be collected for urine routine examination and culture. The catheter retention duration will be recorded, and also the first self-urination time, residual urine, pain score, and recatheterization (if any).

For all patients the catheter will be clamped for some time so that the bladder is full when the catheter is removed. The catheter will be pulled out when the desire for urination is at a peak and bladder pressure is increasing. These measures are conducive to the recovery of bladder function and establishment of an effective micturition reflex, which can effectively shorten the time to first micturition after catheter removal.

### Statistical analysis

Continuous variables will be summarized as means (with standard deviation), medians (with Q1–Q3 or interquartile range), and minimum and maximum values. Categorical variables will be expressed as numbers and percentages. The *t* test and Wilcoxon rank-sum test will be used to compare continuous variables, and the chi-square test or Fisher’s exact test to compare categorical variables. Survival analysis will be conducted using the Kaplan–Meier method and the log-rank test. Statistical analysis will be carried out using SAS 9.2. The intention-to-treat principle will be followed during analysis, but patients who develop serious complications in the perioperative period will be excluded. All statistical tests will be two-sided, and *P* ≤ 0.05 will be considered statistically significant.

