**Fig. 1 Fig1:**
[figure not shown]
Flow diagram of enrollment, intervention, and assessment. IPSS International Prostate Symptom Score

The sample size was estimated as follows. According to the latest studies, the incidence of urinary retention after rectal surgery is 25% when the catheter is removed within 2 days after surgery and 10% when the catheter is removed after 7 days. To detect these outcomes with *α* = 0.05 and *β* = 0.2, we would need 100 patients per group (total 200). We decided to enroll 110 patients in each group (total 220), to allow for a possible 10% dropout rate.

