#### Secondary outcome measures

Urinary tract infection occurring following urethral catheter removal.

A midstream urine sample will be taken for microscopy and culture before catheter removal. A urinary leukocyte count ≥ 5 per high-power field for men and ≥ 1 per high-power field for women will be considered as bacteriuria, irrespective of whether or not symptoms of urinary irritation are present. A pure culture of a single organism of > 100,000 colony forming units will be considered a positive culture [2].(2)Urethrorrhagia following urethral catheter removal.

The presence of ≥ 3 red blood cells (RBC) per high-power field will be recorded as urethrorrhagia [2].(3)Anxiety score before operation and on postoperative day 4.

The Zung Self-Rating Anxiety Scale will be used to assess anxiety levels. This is a standard scale for measurement of anxiety, and is mainly used to assess the efficacy of treatments [5].

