### Preoperative evaluation

Preoperative evaluation will include the following:Elicitation of history of previous urinary system disease.Evaluation of bladder function and residual urine by B-mode ultrasonography.Urine routine examination to confirm that there is no pre-existing urinary tract infection or hematuria.

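### Day-4 anxiety is left to an unadjusted two-sample test although the same score is taken before surgery; ANCOVA on the preoperative score would be more precise at no cost

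*Protocol article*

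**What the plan says.** The article fixes its tests by type of variable. In the Statistical analysis section, the *t* "test and Wilcoxon rank-sum test will be used to compare continuous variables"; categorical variables get chi-square or Fisher's exact tests. "All statistical tests will be two-sided". No regression model or covariate is named.

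The Secondary outcome measures section lists "Anxiety score before operation and on postoperative day 4", using a self-rating anxiety scale. Both scores appear under one outcome, and the section does not say whether the groups are compared on day 4 or on the change from before surgery.

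The Preoperative evaluation section also includes "Evaluation of bladder function and residual urine by B-mode ultrasonography". Residual urine above 100 ml is one part of the definition of retention, the primary outcome; need for recatheterization within a day is the other.

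**The concern.** A score taken before randomized treatment, on the same scale as the outcome, usually explains part of the outcome's spread between patients. A two-sample test on the day-4 score leaves that spread in the error term. A two-sample test on the change removes some of it, but adds the noise of the baseline score with a fixed weight of one. ANCOVA estimates the weight from the data.

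The anxiety outcome has some importance here. The Background cites patients' discomfort and anxiety among the reasons behind the guideline's recommendation for earlier removal. On day 4 the early group should have been without a catheter since day 2, while the control group keeps it until day 7. The trial was sized for retention alone, so nothing secures power for anxiety.

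There is a second, smaller cost. With two possible outcome variables (day-4 score or change) and two possible tests (*t* or Wilcoxon), the published text leaves four analyses open for one outcome.

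**Working it through.** **1. The plan's own sample size.** Inputs from the sample-size paragraph under Study design: retention of "25% when the catheter is removed within 2 days after surgery and 10% when the catheter is removed after 7 days", α = 0.05 (two-sided, per Statistical analysis), β = 0.2. Two-proportion formula with pooled variance under the null:

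n = [1.960 × √(2 × 0.175 × 0.825) + 0.842 × √(0.25 × 0.75 + 0.10 × 0.90)]² / 0.15²
= (1.053 + 0.443)² / 0.0225 ≈ 99.5, so 100 per group.

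This matches the stated number exactly, and power at 100 per group is 80.2%. The sample size therefore agrees with an unadjusted comparison of retention and does not depend on any adjustment.

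**2. Anxiety: three possible analyses.** The article gives no standard deviation, effect size or correlation for the anxiety score. Let r be the correlation between the preoperative and day-4 scores, and assume the same variance σ² at both times. The variance of the group difference, relative to a day-4-only comparison, is:

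- day-4 score alone: 1
- change from baseline: 2(1 − r)
- ANCOVA: 1 − r²

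The ratio of ANCOVA to change is (1 − r²) / [2(1 − r)] = (1 + r)/2, which never exceeds 1.

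For power, take 100 per group and, as a benchmark, the effect that gives a day-4-only comparison 80% power: (1.960 + 0.842) × √(2/100) = 0.396 SD.

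| Assumed r | ANCOVA variance factor | Equivalent sample size, 1/(1 − r²) | Power: day 4 only | Power: change | Power: ANCOVA |
|---|---|---|---|---|---|
| 0.3 | 0.91 | 1.10 | 80% | 65.8% | 83.6% |
| 0.5 | 0.75 | 1.33 | 80% | 80.0% | 89.9% |
| 0.7 | 0.51 | 1.96 | 80% | 95.1% | 97.5% |

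Against the change score, ANCOVA's variance is 0.65, 0.75 and 0.85 times as large at the same three correlations. So the gain does not vanish if the change is what the authors intend.

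**3. Retention, for comparison.** If preoperative residual urine explains a share R² of the variation in retention, the effective size is roughly 100/(1 − R²) per group. Power goes from 80.2% to 81.0% at R² = 0.02, 82.2% at 0.05 and 84.2% at 0.10. Simulating 3,000 trials of 100 per group, with a covariate-adjusted risk difference, gave:

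- covariate with no prognostic value: 81.1% unadjusted, 80.6% adjusted
- odds ratio 1.65 per SD: 82.0% and 82.4%
- odds ratio 2.7 per SD: 82.1% and 85.0%

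The change lies between about −1 and +4 points and depends on a prognostic strength that the article does not give.

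**The case against.** The best defence is that nothing stated is wrong. Unadjusted tests are valid under randomization, and chance imbalance is already allowed for in their error rates and confidence intervals. The article is condensed and the SAP is not shown; adjusted analyses are often left to it. This stands as a limit on severity. It does not remove the point, because the article does not stay silent on the method: it names the tests, and a better one is available from data already collected.

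It can also be said that a *t* or Wilcoxon test on the change would use the baseline, and that the text permits it. That is correct, so a reader should not infer that the baseline is certainly ignored. But the change score is at best as precise as ANCOVA in large samples, and at r = 0.3 it is worse than ignoring the baseline.

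Two stronger readings are tempting and are not supported. The first is that the primary analysis also throws away precision because preoperative residual urine is unused. No passage shows that this measure predicts retention. The exclusion of urinary system disease, earlier retention, drugs likely to affect bladder function and prostate disease probably narrows its range, and the gain computed above may be nil. Nor are events sure to be plentiful: the design rates give 25 + 10 = 35 at 100 per group, but the retrospective series in the Discussion (4.8% and 4.7%) would give only 4.8 + 4.7 = 9.5. The second is that randomization is unstratified, so imbalance goes uncorrected. The Randomization and blinding section names no stratification factor, but that silence in a condensed article is not a statement that none is used.

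**Conclusion.** The point holds for the anxiety score alone. Among the listed outcomes it is the one stated to be measured on a continuous scale both before and after surgery; retention, UTI and urethrorrhagia are binary and do not fall under the quoted test. Compared with a day-4-only comparison, ANCOVA reduces variance by 9% to 49% over assumed correlations of 0.3 to 0.7. Compared with a change score, it is never less precise in large samples. These sizes rest on the assumed correlations and on equal variance at the two times, and the power figures also rest on a benchmark effect that the article does not give.

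This is a minor, free improvement to one secondary outcome. It does not make the planned tests invalid, change the sample size or weaken the primary comparison.

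**What to change.** Add one sentence to the Statistical analysis section: the day-4 anxiety score will be compared between groups by ANCOVA with the preoperative score as covariate, and the adjusted mean difference will be reported with its 95% confidence interval. This also settles which form of the outcome is tested. A Wilcoxon test may stay as a sensitivity analysis if skewness is a worry.

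A risk difference for retention adjusted for preoperative residual urine may be prespecified as a supporting analysis beside the chi-square test, but it is optional and its gain is small or uncertain.

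The cost is one degree of freedom in a comparison of about 200 patients. No new data, visits or patients are needed. The sentence should be fixed before outcome data are examined.

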#### Exit criteria

Rectal cancer surgery is combined with additional pelvic surgery (including pelvic lymph node dissection, hysterectomy, salpingo-oophorectomy, posterior vaginectomy, cystectomy, ureteral double-J stenting, ureterectomy, ureteroureterostomy, prostatectomy).There is significant intraoperative damage to the pelvic nerve (patients classified as type IV by the Sugihara standard).Postoperative Clavien–Dindo grade III or VI complications.

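### The plan claims intention-to-treat but excludes randomised patients with serious perioperative complications, so the primary comparison rests on a modified set that a post-randomisation event defines

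*Protocol article*

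**What the plan says.** Four places in the protocol article bear on who is analysed.

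- **Statistical analysis:** "The intention-to-treat principle will be followed during analysis, but patients who develop serious complications in the perioperative period will be excluded". Neither the seriousness of the complication nor the length of the perioperative period is defined there.
- **Exit criteria:** three grounds for exit are listed: additional pelvic surgery, type IV pelvic nerve damage at operation, and "Postoperative Clavien–Dindo grade III or VI complications". The section does not say whether a patient who exits is still followed or analysed.
- **Grouping:** "After urethral catheter placement the participants will be randomly assigned to either the experimental arm or the control arm". The catheter comes out on postoperative day 2 in the experimental arm, while "participants assigned to the control group will have their urethral catheters removed on postoperative day 7".
- **Study design, sample-size paragraph:** 100 per group is raised to 110 "to allow for a possible 10% dropout rate". What counts as dropout is not stated.

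**The concern.** An intention-to-treat analysis keeps every randomised patient in the assigned arm. A rule that removes patients for something that happens after allocation gives that up, and with it the guarantee that the compared groups differ only by chance and by treatment.

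Here the removal need not be neutral. From postoperative day 2 the arms differ in catheter exposure, so complications after that point arise under different conditions. The outcome also becomes known at different times. Retention is defined "with need for recatheterization within 1 day of removal of the urethral catheter", which means by about day 3 (2 + 1) in the early arm and about day 8 (7 + 1) in the control arm. A complication between those days would remove an early-arm patient whose outcome has been seen, but a control patient whose outcome has not.

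At stake is the primary comparison itself, and a report that carries the intention-to-treat label for a set that does not meet it.

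**Working it through.** **1. Order of events.** Grouping puts the epidural first, then the urethral catheter, then randomisation. Postoperative complications therefore follow randomisation. As the sequence is described, so do intraoperative events, including the other two exit grounds. Those two are settled at the operation, before catheter exposure differs, so they are less likely than the complication rule to depend on arm. They still concern randomised patients.

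**2. The plan's own sample size.** Inputs from Study design: 25% versus 10%, α = 0.05, power 80%. The test is two-sided (Statistical analysis) and allocation is 1:1 (Randomization and blinding). With pooled variance and mean rate (0.25 + 0.10)/2 = 0.175:

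n = [1.960 × √(2 × 0.175 × 0.825) + 0.842 × √(0.25 × 0.75 + 0.10 × 0.90)]² / 0.15²
= (1.053 + 0.443)² / 0.0225 ≈ 99.5, so 100 per group.

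This matches the plan. The step to 110 is 100 × 1.1.

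**3. Power at the number analysed.** Power = Φ[(0.15√n − 1.053)/0.527].

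| Situation, per arm | n analysed | Power |
|---|---|---|
| All 110 analysed | 110 | 83.8% |
| 10% lost in total, exclusions inside it | 110 × 0.90 = 99 | 79.8% |
| 10% dropout, then 5% excluded | 99 × 0.95 ≈ 94 | 77.7% |
| 10% dropout, then 10% excluded | 99 × 0.90 ≈ 89 | 75.4% |

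The 5% and 10% exclusion rates are assumptions, since the protocol gives none. To keep 100 evaluable per arm in the last two rows, enrolment would have to be 100/(0.90 × 0.95) ≈ 117 and 100/(0.90 × 0.90) ≈ 124 per arm.

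**4. Bias (assumed figures).** Let true retention be p = 15% in both arms, so there is no treatment effect. Let r = 40% be the retention rate among excluded patients and e the fraction excluded. Retention in the analysed set is (p − e·r)/(1 − e):

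- e = 5%: (0.15 − 0.02)/0.95 = 13.7%
- e = 10%: (0.15 − 0.04)/0.90 = 12.2%
- e = 15%: (0.15 − 0.06)/0.85 = 10.6%

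| Excluded, early vs control | Analysed retention | Spurious difference |
|---|---|---|
| 5% vs 10% | 13.7% vs 12.2% | 1.5 points |
| 5% vs 15% | 13.7% vs 10.6% | 3.1 points |
| 10% vs 10% | 12.2% vs 12.2% | 0 |

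Swapping the arms reverses the sign. Even in the last row both rates are understated, at 12.2% against a true 15%.

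**The case against.** The contradiction is hard to dispute, but several stronger readings go further than the document allows.

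- **Lost patients not budgeted for.** A reader might infer that the exclusions fall outside the sample size. Study design leaves dropout undefined, so they may sit inside the 10%, and a total loss of 10% still leaves 79.8% power. Only the ambiguity is established.
- **Exclusion by staff who know the allocation.** Randomization and blinding says surgeons cannot be blinded and that results are assessed by blinded independent researchers. No section says who applies the exclusion, so unblinded application is possible but not stated.
- **The exclusion would overturn the result.** Counts can be chosen to show this: 22/110 versus 11/110 gives P = 0.038, and removing 6 early-arm patients (4 with retention) and 4 control patients (none) gives 18/104 versus 11/106, P = 0.146. But if half of the same 6 and 4 had retention, the result is 19/104 versus 9/106, P = 0.037. The shift comes from the lopsided choice, so it is no measure of the harm.
- **Timing alone as bias.** An outcome seen earlier in one arm does not distort the comparison unless exclusion also depends on arm or outcome. The Discussion links retention to recatheterisation and infection risk. It does not link either to complications serious enough to trigger exclusion. The mechanism is plausible but not documented.
- **Two different complication sets.** The general phrase in Statistical analysis may be shorthand for the exit criterion, and the non-consecutive grades listed there may be a transposition. This is a matter for clarification.

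All of this limits the size that can be claimed. It leaves intact that a stated rule removes randomised patients because of a later event.

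**Conclusion.** The concern holds. The analysis population is wrong as written: it is called intention-to-treat but is a modified set conditioned on a post-randomisation event. Bias in the retention comparison is possible, not demonstrated. In the illustration it is 1.5 to 3.1 points when exclusion differs between arms by 5 to 10 percentage points, and zero when exclusion is equal. Those figures rest on assumed retention of 15% overall and 40% among excluded patients, the same in both arms.

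The effect on power is secondary and conditional: about 79.8% if the 10% allowance covers all losses, and about 77.7% or 75.4% if exclusions add 5% or 10%. The case for change does not depend on it, because conditioning on a later event can bias the comparison at any sample size.

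**What to change.** 1. In Statistical analysis, delete the clause that excludes patients with serious complications. Make the primary analysis of retention all randomised patients in their assigned arm, including those who meet any of the exit criteria.
2. State that recatheterisation and urine results continue to be recorded after exit.
3. State how patients whose outcome cannot be assessed are counted, and fix that rule before the data are examined by arm.
4. Keep the complication-excluded set as a labelled sensitivity analysis.
5. Reconcile the complication wording in Exit criteria and Statistical analysis so that both name the same events. The clinical exit rules themselves remain with the investigators.
6. In the sample-size paragraph, say what the 10% allowance covers.

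The cost is mainly wording. Outcomes must still be collected for inpatients who exit; the Detailed description of procedure already provides for recording recatheterisation and urine tests. The estimated effect may be slightly diluted by patients who did not follow the assigned timing. Against that, fewer patients are lost from the analysis: with all 110 per arm analysed, power at the design rates is 83.8%.
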